### Randomization

All community hospitals in the four districts will be numbered. Then using computer-generated random numbers, community hospitals will be chosen at random. We will use the community health records management system of Xi’an city to export older adults’ health information of community hospitals and order from 1 to n. Corresponding older people through random number software generating 400 numbers will be selected as a sample. After the older adults are recruited, medical students will choose eligible participants and complete informed consent. Using the knowledge, attitudes, and practices (KAP) questionnaire, baseline information will be collected. On account of balancing the baseline, the clusters will be grouped in the intervention and control group randomly through randomization design and Chi-square test.

### Data analysis

Epidata 3.1 will be employed to input data with the help of two investigators. All data collected will be stored on a password-protected computer. Descriptive statistics will be used to present the sociodemographic characteristics of the participants as mean ± standard deviation (M ± SD) and percentage. The chi-square test will be used to compare the difference between vaccination uptake and the correct knowledge rate between the intervention group and the control group before and after the intervention. The t-test will be employed to check the difference in scores of knowledge, attitude, and behavior. A significance level of 5% will be selected in every estimate. The SPSS version 21.0 will be used to perform all analyses.

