## Methods

### Study design

This is a CONSORT-compliant cluster randomized controlled trial that will determine the effectiveness of video-led counseling to older adults about influenza and influenza vaccination by medical students [28]. Stratified cluster-based sampling will be employed in this study. Based on the socioeconomic status of every district in Xi’an city, Shaanxi Province, four districts will be selected out of 13, including two districts that have high socioeconomic status, including Xincheng and Yanta, and two districts that have low socioeconomic status, including Chang’an and Baqiao. Two community hospitals will be chosen randomly from each district using computer-generated random numbers. In total, 8 community hospitals will participate in this trial (4 hospitals of intervention and 4 hospitals of the control group). The older adults will be chosen randomly by the health management system of Xi’an city. The Chinese guidelines recommend vaccination should preferably be completed by the end of October. If people do not receive the vaccine at that time, vaccination will be available throughout the flu season. Therefore, the intervention period (six months) will have two stages. One is before the flu season (August, September, October), and one is during the flu season (November, December, January).

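### Eight hospitals are randomised, but the named chi-square and t-tests treat participants as independent, so the 5% level is not kept if the ICC is above 0

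*Protocol article*

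**What the plan says.** Under Study design the article states: "This is a CONSORT-compliant cluster randomized controlled trial". The same section fixes the number of clusters: "In total, 8 community hospitals will participate in this trial (4 hospitals of intervention and 4 hospitals of the control group". Under Randomization the hospital is again the allocated unit: "the clusters will be grouped in the intervention and control group randomly through randomization design and Chi-square test".

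The Data analysis section gives one test for binary outcomes: "The chi-square test will be used to compare the difference between vaccination uptake and the correct knowledge rate between the intervention group". It gives one for the scores: "The t-test will be employed to check the difference in scores of knowledge, attitude, and behavior". The error level is set for everything: "A significance level of 5% will be selected in every estimate". SPSS is to perform all analyses. No hospital effect, mixed model, GEE, robust variance or hospital-level summary is mentioned. The Sample size section has no ICC or design effect, so clustering is not allowed for there either.

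**The concern.** The unit of analysis does not match the unit of randomisation. Two people attending the same hospital are likely to resemble each other more than two people from different hospitals. The article gives reasons to expect this: the districts were picked because they differ in socioeconomic status, and the sessions are held in the hospitals in small groups. When outcomes are correlated within hospitals, the comparison of arms carries between-hospital variation that an individual-level test leaves out. Its standard error is then too small.

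Vaccination coverage is a primary outcome. The gain in uptake is also the effect measure in the planned cost-effectiveness ratio, and the Discussion offers the results to policymakers. A chance difference between one set of four hospitals and another could be reported as an effect of the video.

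**Working it through.** **Inputs.** From the article: 8 hospitals, 4 per arm; 200 participants per group; a stated minimum of 80 per group; uptake of 2% versus 10%; power 0.90; significance level 0.05. Assumed: two-sided testing, equal hospital sizes, and ICC between 0 and 0.05. Equal sizes give 200/4 = 50 per hospital at the planned size and 80/4 = 20 at the stated minimum.

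**The plan's own figure.** The usual two-proportion formula, with mean proportion 0.06, gives n = [1.96·√(2·0.06·0.94) + 1.2816·√(0.02·0.98 + 0.10·0.90)]² / 0.08² = (0.658 + 0.424)² / 0.0064, or about 184 per group. The stated 80 is not reproduced. The formula used is only cited, and this is a separate matter. With 200 per group and independence, power is about 92%, so the stated 0.90 can be met at the planned size only if clustering is absent.

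**Design effect.** DE = 1 + (m − 1)·ICC. With m = 50 this is 1.49, 1.98 and 3.45 at ICC 0.01, 0.02 and 0.05. The 200 per arm are then worth 200/DE = 134, 101 and 58 independent participants. The true standard error is √DE = 1.22, 1.41 and 1.86 times the one the named tests use.

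**Large-sample error rate.** A nominal 5% test has real error 2·[1 − Φ(1.96/√DE)]:
- ICC 0.01: 1.96/1.22 = 1.61, giving 10.8%
- ICC 0.02: 1.96/1.41 = 1.39, giving 16.4%
- ICC 0.05: 1.96/1.86 = 1.06, giving 29.1%

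**Simulation with 4 versus 4 hospitals.** Beta-binomial data, 40,000 runs, no true effect. Individual-level chi-square test:

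| Completers per hospital | Uptake | ICC 0 | 0.01 | 0.02 | 0.05 |
|---|---|---|---|---|---|
| 50 | 2% | 4.5% | 9.6% | 14.6% | 25.7% |
| 50 | 10% | 4.8% | 10.6% | 15.8% | 28.9% |
| 20 | 2% | 3.3% | 4.6% | 5.8% | 9.9% |
| 20 | 10% | 4.7% | 7.0% | 9.2% | 15.4% |

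A repeat with 200,000 runs agreed to within half a percentage point. The individual-level t-test on normal scores, 50 per hospital and 10,000 runs, gave 5.0%, 12.2%, 16.2% and 28.7%.

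**Hospital-level alternative.** A t-test on the eight hospital proportions (6 df, 50 per hospital, ICC 0 to 0.05) stayed at 4.5–5.2% for 10% uptake. For 2% uptake it fell from 5.8% at ICC 0 to 2.7% at ICC 0.05, so it is conservative when events are rare and clustered. Its power for 2% versus 10%:

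| Completers per arm | ICC 0 | 0.01 | 0.02 | 0.05 |
|---|---|---|---|---|
| 200 | 82% | 67% | 56% | 36–37% |
| 80 | 45% | 39% | 35% | 26% |

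**The case against.** The strongest reply is that no ICC is given, so the inflation cannot be fixed at one value, and at ICC 0 there is none. A reader might infer that the 5% level is certainly broken. The document supports only the conditional statement.

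The larger error rates also need 50 completers in each hospital. The article raises 80 to 200 per group to allow for loss and low response, and does not say that hospitals are equal in size. At 20 per hospital and 2% uptake the error is below 5% at ICC 0.01. That is limited comfort: the chi-square test starts at 3.3% there because events are few, and it reaches 9.9% at ICC 0.05.

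Three other stronger readings are not supported. A reader might conclude that the trial's confidence intervals are wrong, but the article plans none; one can say only that an interval built on these tests would be too narrow if the ICC is above 0. A reader might extend the chi-square criticism to willingness, the other primary outcome, but the Data analysis section names no test for it. A reader might also assume that one set of students serves each hospital. The article says only that one student educates five older adults. Nor does it say whether the two hospitals in a district are split between arms; if they are, district differences largely cancel.

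An appeal to an unseen analysis plan does not help. The article does not leave the method open; it names tests that do not fit the design.

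**Conclusion.** The Data analysis section is wrong as written and must be changed. Its chi-square test (uptake, correct-knowledge rate) and t-test (knowledge, attitude and behaviour scores) ignore the randomised unit, so the 5% level is not protected against any positive within-hospital correlation. At the planned size an ICC of 0.01 is enough to about double the chi-square error rate. An ICC of 0.05 raises it to between a quarter and three tenths. With 20 completers per hospital the inflation is smaller, but it remains at most ICCs in the range shown. These figures rest on an assumed ICC, equal hospital sizes, two-sided testing and simple allocation of four hospitals to each arm.

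**What to change.** In Data analysis, replace both tests with a comparison of the eight hospital-level proportions (uptake, correct-knowledge rate) or means (scores). Use a t distribution with 6 df and report the difference with its 95% confidence interval. Name the same approach for willingness. State how hospitals were allocated and match the degrees of freedom to it: adjusting for the two socioeconomic levels leaves 5, and an analysis within the four districts leaves 3.

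A mixed or GEE model with hospital as cluster is an alternative only with a named small-sample correction: Satterthwaite or Kenward-Roger degrees of freedom for a mixed model, or a bias-corrected sandwich variance with t critical values for GEE. It may be unstable for uptake, because 2% of 50 is one expected event per control hospital.

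The cost is wording and reanalysis, provided each participant's hospital is recorded; no new data are needed. The real price is power, which falls below the stated 0.90 even at ICC 0 with 200 completers per arm. The power statement under Sample size should therefore be restated for the hospital-level test over a stated ICC range.

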### Sample size

According to previous studies [31], the influenza vaccine coverage among older adults was almost 2% in western China. The relative risk of intervention ranged from 1.04 to 6.22 in the uptake rate compared to the control group. We hypothesized that the influenza vaccine’s uptake rate would increase from 2 to 10% by employing a medical student-led educational intervention. A mathematical formula [32] was used to calculate the minimum sample size. Eighty participants will be required for each group with a study power of 0.90 and a significance level of 0.05. Considering the loss of follow-up and the low response rate, the sample size will be 200 participants for one group.

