### Intervention procedures

The medical students will be recruited from high grades in medical colleges. Screening criteria include 1) those who are well versed in information about various diseases and vaccination; 2) those who could have a better understanding of our study protocol; 3) those who like to educate older adults. Before the formal investigation, medical students will be provided four hours of focused training to increase their understanding of influenza, influenza vaccination, questionnaire items, and video-related professional knowledge. Additionally, a session of training will also be conducted to improve their communication skills, which will help them to better communicate with older adults. The training adequacy of medical students will be conducted through group discussions during which they will be asked to comment directly on their readiness to play their defined role. Any component of the training that will be considered insufficient would subsequently be addressed.

Before the intervention, medical students will call the older adults, enquiring about their willingness to participate in this program. After their verbal agreement, older people in the control and intervention group will fill the questionnaires under the supervision of a medical student. Their knowledge, willingness to accept the vaccine, and uptake rate will be assessed.

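### Baseline scores, willingness and uptake are collected, but the stated between-arm tests do not adjust for them, so part of any baseline difference between 4 + 4 hospitals stays in the estimate

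*Protocol article*

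**What the plan says.** Baseline measurement is described twice in the protocol article. Under Randomization: "Using the knowledge, attitudes, and practices (KAP) questionnaire, baseline information will be collected". Under Intervention procedures, for both groups before the intervention: "Their knowledge, willingness to accept the vaccine, and uptake rate will be assessed".

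Data analysis then names the tests. Vaccination uptake and the correct-knowledge rate are compared by chi-square "between the intervention group and the control group before and after the intervention". For the scores, "The t-test will be employed to check the difference in scores of knowledge, attitude, and behavior". No baseline covariate, change score or difference-in-differences is stated. Willingness, one of the two primary outcomes under Outcome indicators, is given no test by name.

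The design is small in clusters: "In total, 8 community hospitals will participate in this trial (4 hospitals of intervention and 4 hospitals of the control group". One sentence under Randomization addresses balance: "On account of balancing the baseline, the clusters will be grouped in the intervention and control group randomly through randomization design and Chi-square test". It does not name the variables to be balanced, the algorithm or the criterion for acceptable balance.

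**The concern.** The same people answer the same items before and after the intervention, so the baseline value is likely to be the best single predictor of the follow-up value. Under Data analysis it enters, at most, as a separate comparison of the arms. Two tests, one before and one after, do not combine into one effect estimate, and nothing tells the reader how to interpret the second when the arms differ on the first.

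With four hospitals per arm, sound randomisation can still produce a visible baseline difference. An unadjusted follow-up comparison then mixes the intervention effect with whatever part of that difference persists. Adjustment removes most of it and may also narrow the interval, using data the trial already plans to hold.

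**Working it through.** The article gives no figure for expected baseline imbalance, ICC or baseline-to-follow-up correlation, so there is no stated figure to reproduce on this point.

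**Inputs**
- From the article: 4 hospitals per arm (Study design); 200 people per arm (Sample size); 400 sampled (Randomization). Equal hospital sizes give 400/8 = 50 per hospital.
- Assumed: ICC 0.02 and 0.05; correlation r = 0.3, 0.5 and 0.7; simple allocation with no effective balancing; equal SDs at baseline and follow-up.

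**Step 1. Chance baseline difference between arms, in SD units**

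Design effect DE = 1 + (50 − 1) × ICC. SD of the difference = √(2 × DE/200).

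| ICC | DE | SD of difference | 95% range (×1.96) |
|---|---|---|---|
| 0.02 | 1.98 | √0.0198 = 0.141 | ±0.276 |
| 0.05 | 3.45 | √0.0345 = 0.186 | ±0.364 |

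**Step 2. Part that reaches the follow-up comparison**

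Carry-over ≈ r × baseline difference, taking the same slope between hospitals as within them. At the edge of the 95% range:

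| r | ICC 0.02 | ICC 0.05 |
|---|---|---|
| 0.3 | 0.3 × 0.276 = 0.08 SD | 0.3 × 0.364 = 0.11 SD |
| 0.5 | 0.5 × 0.276 = 0.14 SD | 0.5 × 0.364 = 0.18 SD |

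Most allocations would fall inside these edges.

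**Step 3. Precision gain**

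Adjustment multiplies the individual-level variance by 1 − r², which is 0.91, 0.75 and 0.51 for r = 0.3, 0.5 and 0.7. Those are cuts of 9%, 25% and 49%. They apply only to the individual part of the variance of an arm mean. At ICC 0.05:
- individual part: 0.95/200 = 0.00475
- between-hospital part: 0.05/4 = 0.0125
- individual share: 0.00475/0.01725 = 0.275

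If the between-hospital variance does not change, the cut in the variance of the arm difference is 0.275 × 9% = 2.5%, 0.275 × 25% = 7% and 0.275 × 49% = 13%. At ICC 0.02 the two parts are 0.98/200 = 0.0049 and 0.02/4 = 0.0050, a share of about one half, so the cuts roughly halve to 4.5%, 12% and 24%. The gain is larger only if baseline also explains differences between hospitals.

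**Step 4. Coverage**

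Sample size takes baseline coverage as almost 2%, so about 0.02 × 200 = 4 people per arm would have been vaccinated before. A covariate that is the same for nearly everyone can explain little individual variation in later uptake.

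**The case against.** - **Randomisation protects the comparison.** On average it does, and a cluster-correct standard error would allow for chance imbalance. A reader might infer that the unadjusted tests are biased. The article does not support that; what stands is conditional error in the realised allocation and some lost precision. Ignoring hospitals in the standard error is a separate and more serious matter.

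- **The article already intends to balance baseline.** This is fair, and districts were also chosen by socioeconomic status with two hospitals in each. Effective restriction would make the ranges above too wide. But no variables or criterion are named, eight clusters cannot ensure balance, and a non-significant chi-square test does not show it. If clusters are balanced on baseline variables, the analysis should normally adjust for them.

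- **The score test may already use baseline.** The before-and-after wording stands only in the chi-square sentence. The t-test sentence gives no timing and could mean change scores. That ambiguity is real, and for the scores a separate unadjusted comparison is only the natural reading.

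- **Within-arm testing.** A reader might infer that the plan tests each arm before against after with an independent-samples test. The chi-square sentence says the comparison is between the two groups, so that criticism is not supported.

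- **Adjustment can be left to an analysis plan.** This often holds for detail. Here the article names the tests, and a later plan that follows it would inherit them.

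**Conclusion.** The point holds as an improvement to a stated analysis. Baseline values are collected on the same people and, as written, the tests do not adjust for them. The unadjusted comparison remains unbiased on average. In the realised allocation it may carry about 0.08 to 0.11 SD at r = 0.3, or 0.14 to 0.18 SD at r = 0.5, at the edge of the 95% range of baseline imbalance. This assumes ICC 0.02 to 0.05, 50 people per hospital and simple allocation; successful balancing would reduce it.

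It would be tempting to quote ±0.28 to ±0.36 SD as the error in the result, or 9% to 49% as the gain in precision. Neither is right: the first is the baseline difference before multiplication by r, and the second applies to individual-level variance only. At ICC 0.05 the cut in the variance of the arm difference is about 2.5% to 13% unless between-hospital variance also falls. The benefit is mainly for the secondary scores and for willingness, and is small for coverage.

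**What to change.** In Data analysis, state one between-arm comparison per outcome at month 6, adjusted for the person's own baseline value:
- knowledge, attitude and practice: the corresponding baseline score;
- willingness: baseline willingness, with the test now named;
- coverage: prior vaccination, noting that little gain is expected.

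Do this within a cluster-aware analysis. A two-stage method suits eight hospitals: regress the individual outcome on baseline without an arm term, take the mean residual for each hospital, and compare the 4 + 4 means on 8 − 2 = 6 degrees of freedom. If allocation is restricted on named variables, state them and adjust for them, keeping hospital-level covariates to very few. Present baseline values by arm descriptively in place of a separate significance test.

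The cost is analysis wording. No new data are needed, only linkage of each person's baseline and follow-up questionnaires. The change should be made before the month-6 data are compared by arm.

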### Economic evaluation

The economic evaluation will be performed, referring to WHO’s cost-effectiveness and strategic guideline (WHO-CHOICE) [38, 39]. Compared with no intervention, the incremental cost will consist of program costs and intervention costs [39]. The expense of project administration, including connecting with community hospitals, the older adults, and medical students’ salary, will be considered an incremental cost in this study. Incremental health effects deprive of the improvement of uptake of influenza vaccine. The incremental cost-effectiveness ratio will be calculated to judge whether it is economical.

### Ethical statement

Xi’an Jiaotong University’s Research Ethics Committee has approved this study (No. 2020–1183). The written informed consent of the participants will also be obtained during the investigation.

## Discussion

To increase the influenza vaccination rate of older adults, our study will offer 12 min of video intervention and 15 min of group discussion with older adults on the management of medical students. A self-designed KAP questionnaire will be used to assess the difference between knowledge, attitudes, and practice between the intervention group and the control group. The exploratory study could give reference to devise the influenza immunization strategy. To our knowledge, this intervention method combining educational video, medical students with a small group discussion was not used in previous research.

A few intervention studies improving influenza vaccination uptake in older adults were conducted in the Chinese mainland. One study conducted in Ningbo of China [40] showed an increase in the uptake rate and a decrease in the outpatient of upper respiratory tract infection (URI) through comprehensive intervention measures, which included improving the knowledge of the physician, nurses, and older adults, establishing a temporary vaccination point and improving relevant policies. Recommendations by health workers and increasing vaccination sites were the intervention measures employed in the study in Ningbo [41], which revealed that it could promote vaccine coverage.

In the public health system, clinical practitioners often remain busy due to facing the enormous demands of patients [42], so they do not have enough time to educate them. From an economic perspective, the cost of clinic promotion intervention is high, as indicated in a systematic review [43]. Medical students have more free time compared with physicians, nurses, and pharmacists. Every summer or winter vacation Chinese authority requires undergraduates, including medical students, to conduct research or spread scientific knowledge to the public [44]. The video could also be standardized, so it is possible to implement this intervention in a larger area in the future with the cooperation of the health system.

Those medical students who had a 3 min face-to-face education with older people with pamphlets gained a significant increase in the influenza vaccination rate in the Hong Kong study [26]. In our study, the video could be comprehended easily by older adults, as noted in a previous study [25], and 15 min discussion will help them grasp knowledge and reduce their vaccine hesitancy.

With the development of socioeconomic status, older adults pay more attention to their quality of life. It was mentioned to build a lifelong learning system for older people in China’s strategy planning toward the aging problem in 2019. Senior Citizens’ Universities (SCUs) could be a carrier to spread scientific knowledge [45]. In the future, our study will expand on how to conduct health education about influenza in SCUs.

Vaccination policy [31], mostly free vaccination toward influenza [46], can influence the rate according to some studies. Currently, people still need to pay for the influenza vaccine out of pocket in most of the places in China [27, 46]. The government could list it as one of the free vaccines to promote the uptake rate in the future.

Our study has several strengths. First, this study uses medical students to intervene that is cost-effective and can enhance educational effectiveness. Second, the intervention approach of our study is suitable for older adults (urban and rural) due to a video being easy to understand. Third, our study will act as a reference for policymakers to implement influenza vaccination for health authorities. However, there are some limitations to this study. First, the trial will only last 6 months, which can improve older adults’ knowledge to some extent, but the time may not be enough to change the attitude and behavior of older adults. Second, the study’s generalizability will be limited as the study will be undertaken in one city due to limited time, response burden, and inadequate funding. However, this study could be conducted on a large scale if our intervention gets successful results.

